## Abstract

**Background:**

Care management programmes are an effective approach to care for high risk patients with complex care needs resulting from multiple co-occurring medical and non-medical conditions. These patients are likely to be hospitalized for a potentially "avoidable" cause. Nurse-led care management programmes for high risk elderly patients showed promising results. Care management programmes based on health care assistants (HCAs) targeting adult patients with a high risk of hospitalisation may be an innovative approach to deliver cost-efficient intensified care to patients most in need.

**Methods/Design:**

PraCMan is a cluster randomized controlled trial with primary care practices as unit of randomisation. The study evaluates a complex primary care practice-based care management of patients at high risk for future hospitalizations. Eligible patients either suffer from type 2 diabetes mellitus, chronic obstructive pulmonary disease, chronic heart failure or any combination. Patients with a high likelihood of hospitalization within the following 12 months (based on insurance data) will be included in the trial.

During 12 months of intervention patients of the care management group receive comprehensive assessment of medical and non-medical needs and resources as well as regular structured monitoring of symptoms. Assessment and monitoring will be performed by trained HCAs from the participating practices. Additionally, patients will receive written information, symptom diaries, action plans and a medication plan to improve self-management capabilities. This intervention is addition to usual care.

Patients from the control group receive usual care.

Primary outcome is the number of all-cause hospitalizations at 12 months follow-up, assessed by insurance claims data. Secondary outcomes are health-related quality of life (SF12, EQ5D), quality of chronic illness care (PACIC), health care utilisation and costs, medication adherence (MARS), depression status and severity (PHQ-9), self-management capabilities and clinical parameters. Data collection will be performed at baseline, 12 and 24 months (12 months post-intervention).

**Discussion:**

Practice-based care management for high risk individuals involving trained HCAs appears to be a promising approach to face the needs of an aging population with increasing care demands.

**Trial registration:**

Current Controlled Trials ISRCTN56104508

## Background

Healthcare systems are challenged by an increasing number of patients with multiple chronic conditions [1]. Individuals with multiple chronic conditions are more likely to be at risk for functional impairment [2] and adverse drug events [3]. Self management capabilities decline with an increasing number of co-occurring medical conditions [4]. In addition, medical care for patients with multiple chronic conditions is often fragmented by poor coordination between different healthcare providers [5]. These patients are more likely to be hospitalised for a potentially 'avoidable' cause (e.g., unmanaged exacerbation, intermittent infection or falls, imperfect transitional care), leading to suboptimal health outcomes [6] and substantial healthcare costs [7].

Particularly primary care faces a challenge to care for patients with multiple chronic conditions on the background of limited human and restricted financial resources [8,9]. Different suggestions are available to take up the challenge by re-organising the delivery of chronic illness care [10,11]. Based on these concepts, care management interventions have been developed and evaluated focusing on patients with multiple chronic conditions. These interventions share four core elements [12]: (a) comprehensive assessment of patients' medical and non-medical needs and resources, (b) implementation and monitoring of individualised, evidence-based care plans, (c) coordination of services between providers of medical and social care, and (d) enhancement of self-management capabilities among patients and caregivers. Despite positive effects on quality of care and patients' quality of life, the effect on healthcare utilisation and costs remains heterogeneous [9]. Care management interventions have shown to be effective and efficient if they focus on patients with high risk of healthcare utilization [9,13].

It is crucial to identify the patients most likely to benefit from care management programs (case finding). Based on insurance claims data, so called predictive models can be used to identify patients at high risk for future health care utilization [14]. However, not all high risk patients are able and willing to participate in care management programs. Thus, case finding by predictive modelling should be complemented by the treating physician who can identify high risk patients most likely to participate in and benefit from care management [15].

In Germany, chronic heart failure (CHF), chronic obstructive pulmonary disease (COPD), and type 2 diabetes mellitus (DM) were among the 20 most frequent causes for hospital admission in 2009 [16]. All three conditions are 'ambulatory care sensitive conditions' (ACSC), meaning that primary care plays an important role in preventing hospital admissions for these conditions [17]. These hospitalisations may be avoidable by coordinated and structured chronic care. Based on exploratory studies, we developed a primary care practice-based care management intervention for patients suffering from any of these index conditions with a high likelihood of hospitalization as predicted by a statistical model [18]. Nearly all of these patients suffer from significant co-morbidities [19,20]. The care management intervention is designed to account for the complex care needs resulting from these co-morbidities.

Chronic care in Germany is mainly delivered by small primary care practices: The practice team usually consists of one or two physicians (general practitioner or general internist) and a small number of healthcare assistants (HCAs), who perform few clinical tasks. HCAs are trained in a three-year part-time curriculum in practice (3920 hours) and vocational school (840 hours). Despite some recent attempts to involve HCAs in chronic care [21], their work is mostly focused on clerical work (including reception) and routine tasks like blood sampling or electrocardiogram recording. However, recent trials on primary care-based disease-specific case management interventions involving trained HCAs showed promising results in patients with osteoarthritis, [22], depression [23] and systolic heart failure [24]. Moreover, practice teams experienced the expanded role of HCAs as valuable resource to enhance the provision of chronic care [25-27].

### Novel aspects of PraCMan

Whereas international research on care management has mainly focused on nurse-led programmes, evidence on the potential role and effects of HCAs in chronic care is scarce. As cost-efficiency of intensified care programs appears to be essential for further implementation, HCA-based programmes may offer an opportunity to deliver intensified care with lower staff costs.

The limited medical education of HCAs could be a potential problem in the care for high-risk patients with multiple chronic conditions and needs to be addressed when designing HCA-based programs. Therefore, PraCMan focuses on three index conditions (DM, CHF, COPD) and distinct comorbidity patterns which we could explore to be common in a population of patients at high risk for future hospitalization [28]. Furthermore, structured written protocols for assessment and monitoring are feasible tools for HCA-based care management programs [29,30]. We designed a modular concept of structured monitoring lists that can be applied either by phone or in the practice. This concept accounts for index conditions as well as for frequent comorbidities.

As case finding has shown to be crucial for the success of intensified care programs, we selected a statistical model based on insurance claims data that predicts future hospitalization instead of costs. A significant proportion of these hospitalizations account for "actionable costs" as they appear to be potentially avoidable. This predictive model proved to be useful to identify patients in need for intensified care [15].

Primary care practice-based care management for patients with either DM, COPD or CHF and a high predicted risk for future hospitalization involving HCAs is a promising approach for effective and cost-efficient intensified care for the patients most in need. This paper describes aim and methods of the PraCMan trial.

## Methods/Design

### Primary objective

The primary objective of this study is to determine whether a primary care practice-based care management intervention will reduce the number of all-cause hospitalizations as compared to standard care. The intervention focuses on patients at high risk for future hospitalizations suffering from DM, COPD, CHF or any combination of these index conditions. The intervention is additional to usual care.

### Secondary objectives

We will explore effects on re-admissions, disease-specific admissions, hospital days, mortality, health-related quality of life, self-management capabilities, medication adherence, physical outcome parameters (e.g. NYHA, number of exacerbations, depressive symptoms), patients' satisfaction with medical care, health service utilization and costs. Besides, we will explore the effects of the intervention on work satisfaction of primary care physicians (PCPs) and HCAs as well as practice organization.

### Study design

The study is designed as a prospective two-armed open cluster randomized controlled trial. Randomization at the level of primary care practice was chosen to prevent contamination between intervention and control patients. Blinding of either patients or practice teams was not possible due to the character of the intervention. However, observers will be blinded during data collection regarding primary and secondary endpoints. Patients were randomized in clusters of 15-20 patients per practice (see Figure 1). Each patient was assigned to a care management team (CM team) consisting of one PCP and one HCA. All primary and secondary endpoints will be measured at either practice or patient level at baseline (T0), at 12 months (T1) and 24 months (T2) after randomization.

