### Data collection

After obtaining written informed consent, patients were registered in the study coordinating centre of the Department of General Practice and Health Services Research Heidelberg (Germany) which is responsible for administration, coordination, data management and monitoring (includes database-set up and validation, data entry, coding, and query management).

Patients will be asked to fill in a pseudonymised paper-based questionnaire. PCPs will document additional data from patients' chart and assess the clinical status of the patient (e.g. dyspnoea, blood pressure). Patient questionnaire and chart review will be performed at baseline, 12-, and 24- month follow-up. In addition to these data sources, pseudonymised insurance claims data of participating patients will be obtained from the AOK including data on health service utilisation, medication, diagnosis and costs. All data from patient questionnaires, case report forms and insurance claims will be compiled.

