**Secondary outcomes**		

Sociodemographic data	Single items from German standard questionnaire [44]	PQ

Mortality	Patient chart	CRF/IC

Quality of Life	EuroQol (EQ-5D) [45]	PQ

	Short Form 12 Health Questionnaire (SF 12) [46]	PQ

Quality of Care	Patient Assessment of Chronic Illness Care (PACIC) [47]	PQ

Depression	Patient Health Questionnaire (PHQ9) [48]	PQ

Adherence	Medication Adherence Reporting Scale (MARS) [49]	PQ

Physical Activity	The Rapid Assessment of Physical Activity (RAPA) [50]	PQ

Smoking status	Self developed items	CRF

Self-management CHF	European Selfcare Behaviour Scale (EHFScB) [51]	PQ

Self-management COPD/DM	Self developed instrument	PQ

Medication regimen	Pharmacy data	IC

Healthcare costs	Data from hospital care, ambulatory care, nursing facilities, pharmacies, rehabilitation	IC

Activities of daily living	ADL [52] IADL [53]	CRF

Comorbidity	Cumulative Illness Rating Scale (CIRS) [54]	CRF

Home visits/Practice visits	Self developed items	CRF

CHF decompensation (CHF patients)	Self developed items	CRF

COPD exacerbation (COPD patients)	Self developed items	CRF

Hypoglycaemia (DM patients)	Self developed items	CRF

Body mass index	Weight, Height	CRF

Blood pressure (all patients)	Standardized Measurement in the practice	CRF

Fasting glucose	Patient chart	CRF

Hemoglobin-A1c	Patient chart	CRF

Dyspnoea (CHF and COPD patients)	Current NYHA-classification (CHF patients) or current MRC Dyspnoe Score (COPD patients) [55]	CRF

Forced expiratory volume (COPD patients)	Standardized Measurement in the practice	CRF

PQ: Patient questionnaire, CRF: Case Report Form, IC: Insurance claims data.

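### The stated observer blinding for primary and secondary endpoints can hold only for claims-based outcomes: at 12 and 24 months, 22 of 25 tabulated secondary rows are recorded by unblinded patients or practices

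*Protocol article*

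**What the plan says.** The protocol article, under Study design, describes an open cluster-randomised trial and states: "Blinding of either patients or practice teams was not possible due to the character of the intervention". The next sentence reads: "However, observers will be blinded during data collection regarding primary and secondary endpoints". It does not say who the observers are.

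The Data collection section names those who record the data. For the questionnaire: "Patients will be asked to fill in a pseudonymised paper-based questionnaire". For the case report form: "PCPs will document additional data from patients' chart and assess the clinical status of the patient (e.g. dyspnoea, blood pressure"). The timing is also fixed: "Patient questionnaire and chart review will be performed at baseline, 12-, and 24- month follow-up".

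Table 1, under Secondary outcomes, gives each row one of three source codes: "PQ: Patient questionnaire, CRF: Case Report Form, IC: Insurance claims data". The primary outcome, the count of all-cause hospitalisations, comes from claims. The dyspnoea row is a physician-type rating, "Current NYHA-classification (CHF patients) or current MRC Dyspnoe Score (COPD patients"), and is coded CRF.

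The Randomization section says that allocation was concealed from PCPs until recruitment in their practice was complete, and that they were then told by letter.

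**The concern.** The design section claims a property, blinded observation of secondary endpoints, that the data-collection section appears to rule out. If the people who rate and report are those just described as unblinded, the claim is untrue for the outcomes they record.

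What is at stake is how secondary differences are read. A plausible route to bias exists. In the intervention arm the PCP plans care and sets the content and frequency of monitoring. The healthcare assistant's assessment covers depression, adherence, physical activity and smoking, which are later scored by PHQ-9, MARS, RAPA and the smoking item. Intervention patients are contacted about symptoms every one to six weeks, so exacerbations and hypoglycaemia may be noticed and recorded differently by arm, in either direction. The Discussion gives quality of care, quality of life and self-management as added reasons for health funds to offer the programme. The Statistical analysis section commits to CONSORT reporting, where a blinding statement would be carried forward.

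**Working it through.** The plan gives no figure on this point to reproduce. The check sets the sections side by side and then counts Table 1.

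**Step 1: who knows the arm, and when.** Patients and practice teams are unblinded (Study design). PCPs recruited without knowing their allocation and were told it after recruitment closed (Recruitment of practice sites and patients; Randomization). Baseline collection started together with recruitment, and the teams were trained after randomisation (Timeframe of the study). Baseline ratings were therefore probably made before disclosure. The 12- and 24-month ratings come after it.

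**Step 2: who records what.** The patient fills in the questionnaire (PQ). The PCP documents chart data and rates clinical status (CRF). Claims data (IC) come from the health fund. The article mentions no independent or blinded assessor.

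**Step 3: count of Table 1 secondary rows by source**, taking EQ-5D and SF-12 as separate rows:

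- PQ, 9 rows: sociodemographics, EQ-5D, SF-12, PACIC, PHQ-9, MARS, RAPA, heart-failure self-care, COPD/DM self-management.
- CRF only, 13 rows: smoking, ADL/IADL, CIRS, home and practice visits, CHF decompensation, COPD exacerbation, hypoglycaemia, body mass index, blood pressure, fasting glucose, HbA1c, dyspnoea (NYHA/MRC), forced expiratory volume.
- CRF/IC, 1 row: mortality.
- IC only, 2 rows: medication regimen, healthcare costs.

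Total: 9 + 13 + 1 + 2 = 25. Recorded only by patient or practice: 9 + 13 = 22, and 22/25 = 88%.

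**Step 4: sensitivity of the count.**

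- Quality of life as one row, or sociodemographics left out: 21 of 24.
- Mortality counted as partly CRF: 23 of 25.
- Numerator without the five rows least open to rating bias (sociodemographics, CIRS, body mass index, HbA1c, fasting glucose): 22 − 5 = 17 rows.
- Denominator with five outcomes named in the text but not in Table 1 (re-admissions, disease-specific admissions, hospital days, emergency visits, nursing-home days), assuming all five come from claims: 22/(25 + 5) = 22/30 = 73%.

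Under every choice, most of the listed secondary outcomes are recorded by people who know the arm. One further item outside Table 1, whether an admission was planned or unplanned, comes from chart review and belongs with them.

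**The case against.** The strongest reply is that nobody is misled. The disputed sentence follows directly on the statement that patients and teams are unblinded, the article names the recorders, and Table 1 codes the source of every row. Secondary effects are described as exploratory, and the Statistical analysis section confines confirmatory interpretation to the primary outcome, which comes from claims. This stands as a limit on the consequences. It does not make the sentence true.

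A second reply is that the observers may be coordinating-centre staff who handle pseudonymised data. The article does not say so. Even if it is so, blinding those who enter or code data cannot protect a score already given by someone who knows the arm.

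A third reply is that the row count is a crude measure of exposure to bias. This stands. HbA1c and fasting glucose are values taken from the chart, sociodemographics are not an effect outcome, and the denominator omits secondary outcomes named only in the text. The article also does not say that the PCP personally makes every CRF entry. Blood pressure and spirometry are only located in the practice, although healthcare assistants belong to the same unblinded team.

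A reader might infer that 88% of the secondary evidence is biased, that a favourable secondary difference would be produced by rating alone, or that no efficacy statement may rest on these outcomes. The documents support none of this. They give no information on the size of any rating bias, the share counts rows and not bias, and open self-report is unavoidable in a trial of this kind.

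**Conclusion.** The sentence is wrong as written. At 12 and 24 months, 22 of the 25 tabulated secondary rows are recorded only by unblinded patients or the unblinded practice. The stated blinding can hold only for claims-based outcomes, the primary outcome among them. It cannot hold for judgement-based or self-reported outcomes such as NYHA/MRC, ADL/IADL, exacerbations, blood pressure, SF-12, EQ-5D, PACIC, PHQ-9, MARS and the self-management scales.

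The conclusion rests on the article's own account of who collects the data and on PCPs knowing their allocation by the first follow-up. It does not extend to the primary analysis, and it is not directed at the baseline ratings. Whether claims extraction is itself done without knowledge of arm is not established anywhere apart from the disputed sentence, so it needs confirmation.

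**What to change.** - Limit the blinding sentence in Study design to the primary and other claims-based outcomes, once the sponsor confirms that these are extracted without knowledge of arm. Say who the observers are.
- Add that CRF outcomes (recorded by the practice) and questionnaire outcomes (recorded by the patient) are assessed open-label at 12 and 24 months.
- Mark each Table 1 row as claims-based or open, with mortality shown as mixed. Give a source for the secondary outcomes named only in the text. The planned/unplanned label, taken from chart review, is open.
- In the report, present and interpret differences on the open outcomes as unblinded assessments. No ban on efficacy statements is needed, since confirmatory claims are already confined to the primary outcome.

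The cost is a reworded sentence, one added sentence, one table column and one query to the sponsor. Sample size, visits and procedures do not change. The downside is that the secondary outcomes will look less protected than the present text says.

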**Figure 1 F1:**
[figure not shown]
**Design of the PraCMan trial**. This figure shows design and timeframe of the PraCMan trial.

### Sample size calculation

Sample size was calculated by using the primary endpoint, i.e. the number of all-cause hospitalizations per patient in the 12 months intervention period. Based on data from our pilot study, we estimated a mean number of 0.7 all-cause hospitalizations per patient per year with a standard deviation of 1 [18]. Based on these estimates, a total of 1602 patients (801 per arm) would be required to detect a between-group difference of 0.14 (20% absolute reduction) with a power of 80% and by using a two-sample *t*-test at a 5% significance level (two-sided). An intracluster correlation (ICC) of 0.01 at practice level could be estimated on the basis of data from a comparable intervention study [24]. Assuming an ICC of 0.01 and an average cluster size of 17, we estimated a design effect of D = 1 + (17 - 1) × 0.01 = 1.16. Taking this design effect into account, a total of 110 practices and 1870 patients (55 practices and 935 patients per arm) will be required. Recent intervention studies reported drop-out rates of 6% [31] and 10% [24], respectively. Therefore, assuming a drop out rate of 15%, we aimed to include 2,210 patients and 130 practices.

### Recruitment of practice sites and patients

PCPs were eligible for the study if they were participating in the primary care-centred care contract of the General Regional Health Fund (AOK). Participation in the primary care (PC)-centred care contract is voluntary for physicians and patients. Care within this contract implies a gate keeping role of the PCP, PCP training and feedback regarding evidence based pharmacotherapy and patient benefits such as reduced waiting times in the practice and late afternoon consultation hours.

We invited eligible PCPs in the Federal State of Baden-Württemberg (Germany) by a formal letter to participate in the study. 132 PCPs from 115 practices gave their written consent and were randomized into the study groups. 234 PCPs gave information before randomization that they decline to participate due to lack of time (n = 129), practice organization (n = 16), unattractive reimbursement (n = 7), no interest (n = 2), concerns about funding source (n = 1), health status of PCP (n = 4) and plans about giving-up practice in near future (n = 7). 63 PCPs did not further specify their reason for declined participation, whereas 5 PCPs were not able to recruit study patients and withdrew participation before randomization.

From the study coordinating centre PCPs received a list of potentially eligible patients based on inclusion and exclusion criteria (see below). After validation of their eligibility patients were recruited by participating PCPs who were blinded to their allocation to the study groups. Patients not willing to participate were asked to give a reason for their decision (on a voluntary basis). PCPs were asked to document patients screened, asked and not included as well as the reason for inclusion and exclusion.

